### Data and statistical analysis

Baseline characteristics of the three groups will be compared by ANOVA test for continuous variables and chi-square test for categorical variables. The baseline factors will include age, sex, medication status, psychological and lifestyle characteristics. Our primary end point is the change of anxiety and worry score (BAI and Penn State Worry Scale) from baseline to the end of intervention. Secondary outcomes included the change in scores of CES-D and SF-12. For primary analyses, treatment outcomes will be assessed by ANCOVA, with change in anxiety score as the baseline variable, while the baseline anxiety score and other baseline characteristics that significantly difference between groups will serve as covariates. A two-sided P value of 0.05 or less will be considered be statistically significant. For secondary analyses, the three groups will be simultaneously taken into the analysis of variance model for repeated measures. The baseline measurement of anxiety symptoms and any significant secondary outcome variables will be entered into the model as a covariate as they are considered to be confounders. Analysis will also be performed on an "intention to treat" analysis.

Since there have been no studies on MBCT with an active control that control for contact time and attention, we need to use the only available study on GAD with an active control by Wetherell et al [22] for sample size calculation. The null hypothesis for this study is that there will be no improvement in the outcome measures in the MBCT group relative to other groups and we will test this hypothesis using a one-sided analysis.

Assuming that the average change of mean score of BAI of patients in MBCT is 5.6 (7.4), in the discussion group is 2.0 (7.4) and that in usual care control is 1.1(7.4) with a 1-sided type I error of 5% and 80% power to detect statistical significant differences between the MBCT and psycho-education group as well as MBCT and usual care control, the required sample size is 76 subjects in each group. We set our enrolment target at 228 subjects.

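### The plan gives two incompatible significance rules for the same primary comparisons: two-sided 5% in the analysis paragraph and one-sided 5% in the hypothesis and sample-size paragraphs

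*Protocol article*

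**What the plan says.** All the relevant text is in the protocol article under Data and statistical analysis, in three consecutive paragraphs.

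- **Analysis paragraph.** It names change in BAI and Penn State worry score as the primary end point and ANCOVA as the primary analysis. It then gives the significance rule: "A two-sided P value of 0.05 or less will be considered be statistically significant".
- **Hypothesis paragraph.** The null hypothesis is no improvement in the outcome measures with MBCT relative to the other groups, and "we will test this hypothesis using a one-sided analysis".
- **Sample-size paragraph.** The calculation is made "with a 1-sided type I error of 5% and 80% power to detect statistical significant differences". It covers two pairwise contrasts, one of MBCT with each of the two control arms. The assumed mean BAI changes are 5.6, 2.0 and 1.1, each with 7.4 in brackets. It concludes that "the required sample size is 76 subjects in each group", and "We set our enrolment target at 228 subjects".

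**The concern.** The two rules concern the same comparisons, MBCT against psycho-education and MBCT against usual care. The two-sided sentence directly follows the primary ANCOVA. The one-sided sentence states how the study hypothesis will be tested, so it is more than a planning convention. No text reconciles them.

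At stake is whether the primary threshold is fixed in advance. For any result favouring MBCT with two-sided P between 0.05 and 0.10, the conclusion depends on which sentence is followed, and that choice could be made after the data are seen. An analysis plan that picked one rule would still conflict with the protocol text. In addition, the 80% power is stated for the one-sided test, so it does not describe the two-sided test of the analysis paragraph.

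**Working it through.** **Inputs, all from the sample-size paragraph.** Mean BAI change is 5.6 (MBCT), 2.0 (discussion group, taken to be the psycho-education arm) and 1.1 (usual care). The bracketed 7.4 is read as the SD. The differences are 5.6 − 2.0 = 3.6 and 5.6 − 1.1 = 4.5. The smaller, 3.6, drives the size. Power is 80%, with equal arms. No dropout rate and no adjustment for two contrasts is stated.

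**Step 1: the plan's own figure.** n per arm = 2 × (z_α + z_power)² × (SD/difference)².

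- One-sided 5%, difference 3.6: 2 × (1.645 + 0.842)² × (7.4/3.6)² = 52.3, so 53. The t-test version is also 53.
- One-sided 5%, difference 4.5: 34 (t-test 35).

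The stated 76 is not reproduced. Two routes give exactly 76, and each needs an input that the article does not state:

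- one-sided 5%, 80% power and 30% dropout: 53/0.70 = 75.7, so 76;
- two-sided 5%, 85% power and no dropout: 76.

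**Step 2: the two thresholds at 76 per arm.** SE = 7.4 × √(2/76) = 1.200.

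- One-sided 5%: 1.645 × 1.200 = 1.97 points.
- Two-sided 5%: 1.960 × 1.200 = 2.35 points.

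These use an unadjusted two-group SE. The planned ANCOVA adjusts for baseline, so its thresholds in points will differ, but the disputed range of P values (0.05 to 0.10, two-sided) stays the same.

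**Step 3: chance of landing in the disputed band** (normal approximation, per comparison).

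- True difference 3.6: 0.912 − 0.851 = about 6%.
- True difference 2.0: 2.0/1.200 = 1.67, and P(1.645 < Z < 1.960) for Z centred there is about 12%.

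**Step 4: size and power under two-sided 5%, difference 3.6.**

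- n for 80% power: 2 × (1.960 + 0.842)² × (7.4/3.6)² = 66.3, so 67 (t-test 68).
- Power with 76 evaluable per arm: 3.6/1.200 = 3.00, and Φ(3.00 − 1.96) = about 85%. The one-sided figure is about 91%.
- Dropout at which two-sided power reaches 80%: 1 − 67/76 = 11.8%, or 1 − 68/76 = 10.5% by t-test, so about 11%.
- If 76 already contains a 30% allowance and 53 are evaluable: SE = 7.4 × √(2/53) = 1.437, 3.6/1.437 = 2.50, and Φ(2.50 − 1.96) = about 70%. Restoring 80% at that dropout would need 67/0.70 = 96 per arm.

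**The case against.** The best defence is that the intended rule can be guessed. The two-sided sentence is attached to the primary ANCOVA and is the stricter of the two, while the one-sided wording sits beside the sample-size calculation. Two-sided 5% is therefore the likelier rule for reporting, and the harm is confined to a narrow range of results. That is fair as to likelihood and size. It does not remove the contradiction, because the one-sided sentence says how the hypothesis will be tested.

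Three stronger readings are tempting, and the document does not support them.

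- **That the looser rule leaves the trial too small.** The one-sided rule is the stated basis of the calculation, but 76 does not follow from it, and 76 exceeds the 67 to 68 evaluable per arm that the two-sided rule needs.
- **That the target is therefore safe.** This holds only if 76 contains no hidden dropout allowance and dropout stays at or below about 11%. The article gives no rate, and its Limitations section expects higher attrition in usual care.
- **That one-sided testing against an active CBT-based comparator is wrong in itself.** A one-sided test could not declare MBCT significantly worse, but the estimate would still be reported. The primary objective is superiority, for which a directional hypothesis is not in itself an error. The contradiction stands without this argument.

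**Conclusion.** The contradiction stands and should be corrected, because the primary decision threshold is not uniquely defined. It affects results favouring MBCT with two-sided P between 0.05 and 0.10. The chance of such a result is about 6% per comparison if the planned 3.6-point difference is true, and about 12% if the true difference is near 2 points. The 5% and 2.5% false-positive rates favouring MBCT are also per comparison. The plan names two primary scores and powers two contrasts, so they are not trial-wide rates.

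The figures assume an SD of 7.4, equal arms and an unadjusted comparison of two groups. Whether 76 per arm keeps 80% two-sided power cannot be settled from the article: power is about 85% if all 76 are evaluable and about 70% if only 53 are. Neither adequacy nor a shortfall should be inferred until the origin of 76 is stated.

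**What to change.** Delete the one-sided test from the hypothesis paragraph and the one-sided 5% error from the sample-size paragraph. State two-sided 5% for hypothesis, analysis and sample size.

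Restate the sample-size paragraph on that basis with all inputs shown: difference 3.6, SD 7.4, two-sided 5%, 80% power, and 67 to 68 evaluable per arm. Add that 76 evaluable per arm give about 85% power per comparison without multiplicity adjustment. Say how 76 arose, including any dropout allowance, and whether alpha is adjusted for the two contrasts. Halving alpha for them would raise the need to 81 per arm (82 by t-test), above 76.

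If the dropout allowance exceeds about 11%, restate the power actually available and do not claim that 80% is kept.

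The change to the rule is one of wording. Its cost is a less favourable stated power, about 85% against 91% at 76 evaluable per arm. The enrolment target comes into question only if the restated inputs show a shortfall that the sponsor wishes to make up.

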## Outcome measures

These will be measured at baseline and at 8 weeks (end of intervention) and will be repeated at 3 months and 6 months and 9 months after intervention.

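### The repeated-measures ANOVA named for follow-up relies on sphericity, which the visit schedule makes doubtful; uncorrected, its group-by-visit test could run at about 5.3% to 7.3%

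*Protocol article*

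**What the plan says.** In the protocol article, Data and statistical analysis, the primary analysis is an ANCOVA of change from baseline to the end of the intervention. For the secondary analyses, "the three groups will be simultaneously taken into the analysis of variance model for repeated measures". On covariates it adds: "The baseline measurement of anxiety symptoms and any significant secondary outcome variables will be entered into the model as a covariate". With baseline as a covariate, the repeated levels are the four post-baseline visits. Under Outcome measures, these are the 8-week visit at the end of the intervention and assessments that "will be repeated at 3 months and 6 months and 9 months after intervention". The significance rule is general: "A two-sided P value of 0.05 or less will be considered be statistically significant".

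The primary and secondary objectives are all set at 9 months, while the primary end point stops at the end of the intervention. The repeated-measures ANOVA is therefore the only named model that covers the time point of the objectives.

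The article does not mention a covariance structure or a sphericity correction. It also names no specific group-by-visit test and no contrast between visits.

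**The concern.** A univariate repeated-measures ANOVA tests visit and group-by-visit against one pooled within-person error. That F test has its nominal level only under sphericity, meaning that the difference between any two visits has the same variance. Equal variances with equal correlations are sufficient for this, but not necessary.

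The post-baseline visits lie 3 to 9 months apart. Symptom scores 3 months apart usually agree more closely than scores 9 months apart. If so, the pooled error is too small for long-span differences and too large for adjacent visits. The problem is separate from missing visits, covariate selection and clustering by class, and it would remain with complete data and independent participants.

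At stake are statements that the arms follow different courses, or that a benefit is kept or lost between the end of the course and 9 months. They would be judged at 0.05 while the true error rate is higher.

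**Working it through.** **The plan's own figures.** The article gives no error rate for this model beyond the general two-sided 0.05, so there is none to reproduce. The group size is as stated: "the required sample size is 76 subjects in each group". The stated inputs (difference 5.6 − 2.0 = 3.6, SD 7.4, one-sided 5%, 80% power) give 2 × (1.645 + 0.842)² × 7.4² / 3.6² ≈ 52.3, so 53 per group rather than 76. That is a separate matter. The check uses 76 as the planned size and does not depend on how it was reached.

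**Inputs.** From the article: three arms of 76, four post-baseline visits (0, 3, 6 and 9 months after the course), nominal 5%. Assumed: complete data, no treatment effect, equal variance at each visit, and three correlation patterns:
- equal: 0.6 between all visits;
- mild decay: a stable person effect plus a fading part, giving 0.5 + 0.3 × 0.6 = 0.680 at 3 months, 0.5 + 0.3 × 0.36 = 0.608 at 6 and 0.5 + 0.3 × 0.216 = 0.565 at 9;
- serial: r per 3 months, so r, r² and r³, with r from 0.5 to 0.9.

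**Step 1: the long-span contrast by hand.** Four visits have three pairs 3 months apart, two pairs 6 months apart and one pair 9 months apart. With variance 1, the pooled error estimates 1 − (mean correlation). The true variance of a change between two visits, relative to what the pooled error assumes, is

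ratio = (1 − correlation of that pair) / (1 − mean correlation),

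and the actual two-sided level is about 2 × [1 − Φ(1.96 / √ratio)].

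- Serial 0.6: mean = (3 × 0.6 + 2 × 0.36 + 0.216) / 6 = 0.456. End of course to 9 months: 0.784 / 0.544 = 1.441, √ = 1.200, 1.96 / 1.200 = 1.633, level about 10.3%. Adjacent visits: 0.4 / 0.544 = 0.735, level about 2.2%.
- Serial 0.8: mean = (2.4 + 1.28 + 0.512) / 6 = 0.699. Long span: 0.488 / 0.301 = 1.62, level about 12.4%. Adjacent: 0.2 / 0.301 = 0.664, level about 1.6%.
- Mild decay: mean = (2.04 + 1.216 + 0.565) / 6 = 0.637. Long span: 0.435 / 0.363 = 1.198, level about 7.3%. Adjacent: 0.32 / 0.363 = 0.881, level about 3.7%.
- Equal correlation: ratio 1, level 5%.

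**Step 2: simulation.** 8,000 null trials per pattern; Monte Carlo standard error √(0.05 × 0.95 / 8000) = 0.24 points at 5%. Epsilon is the Greenhouse-Geisser measure, equal to 1 under sphericity.

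| Pattern | Epsilon | Group-by-visit, uncorrected | Greenhouse-Geisser | Group main effect | 9 months vs end of course, pooled error | 9 vs 6 months, pooled error |
|---|---|---|---|---|---|---|
| Equal 0.6 | 1.00 | 5.5% | 5.3% | 5.2% | 5.1% | 4.9% |
| Mild decay | 0.96 | 5.3% | 5.0% | 5.1% | 7.1% | 3.4% |
| Serial 0.5 | 0.86 | 5.7% | 4.7% | 4.7% | 9.2% | 2.4% |
| Serial 0.6 | 0.81 | 6.0% | 4.6% | 4.9% | 9.7% | 2.5% |
| Serial 0.7 | 0.77 | 6.7% | 5.1% | 5.2% | 11.9% | 2.1% |
| Serial 0.8 | 0.72 | 6.9% | 5.0% | 5.3% | 12.7% | 1.8% |
| Serial 0.9 | 0.68 | 7.3% | 5.0% | 5.2% | 12.6% | 1.4% |

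The uncorrected test is exact under equal correlation, so the 5.5% in the first row is simulation noise. The 5.3% under mild decay likewise cannot be told from 5%. The simulated contrast levels agree with Step 1 within simulation error.

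**Step 3: variations.** A separate simulation with baseline as covariate and the BAI entry cut at 19 gave 5.9% and 6.6% for group-by-visit, and 8.7% and 11.5% for the long-span contrast, at serial 0.6 and 0.8. With its own error term the contrast ran at 5.1%. The between-arm comparison at 9 months stayed at about 5%. Treating baseline as a fifth repeated level raises the uncorrected group-by-visit test to 6.9% to 8.5% under serial correlation, but the article enters baseline as a covariate, so those figures are not the relevant ones.

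**The case against.** The strongest reply is that the article names a family of models and does not say that the F test goes uncorrected. An epsilon correction is a routine option, it fits the quoted sentence, and it restores about 5%. A condensed article may leave such detail to a full protocol or analysis plan. This stands: the missing correction is not in itself an error. What remains is that the named model has a restrictive assumption that suits this schedule poorly, and that a better standard model is available at little cost.

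A reader might infer that the follow-up tests exceed 5% as a matter of fact. The documents do not support that. The excess needs both an uncorrected test and decaying correlation, and the article states neither. Under equal correlation the level is 5%, and under mild decay the omnibus test is barely moved.

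A reader might also infer that the 9-month objectives themselves are tested at an inflated level. They are not. Those objectives concern effects at 9 months, the primary one as a comparison between arms, and the between-arm comparison at that visit keeps about 5%. The contrast between end of course and 9 months has the largest inflation but is not a planned test. Group-by-visit is a standard term of the model, but the article does not single it out. Nor is all the error in one direction, since adjacent-visit contrasts are conservative.

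**Conclusion.** The point holds conditionally. If the ANOVA is run without a sphericity correction and correlation falls with time between visits, the group-by-visit test runs at about 5.3% to 7.3% with 76 per arm, complete data and four post-baseline visits. A pooled-error contrast of 9 months with end of course, if made, runs at about 7% to 13%, and adjacent-visit contrasts at about 1.4% to 3.4%. All these figures rest on assumed correlations. The group main effect, the between-arm comparison at 9 months and the primary ANCOVA keep their level. Severity is minor to moderate: the analysis is secondary and the omnibus excess is at most about 2.3 points (7.3 − 5.0), but no other named model reaches the time point of the objectives.

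**What to change.** In Data and statistical analysis, replace the repeated-measures ANOVA with a likelihood-based repeated-measures model that has visit as a categorical factor, arm-by-visit terms, the baseline score as covariate and an unstructured within-person covariance. Report the arm difference at 9 months from it, which ties the model directly to the stated objectives.

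If the ANOVA is kept, state that visit and group-by-visit P values are Greenhouse-Geisser corrected, and that each between-visit contrast uses its own error term rather than the pooled one.

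The cost is a sentence or two of text and a standard software option, with no new participants, visits or data. The downside is slightly larger P values and wider intervals for long-span comparisons.

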### Secondary objectives

The secondary objectives of this study are to evaluate the effects of MBCT on:

• Patients' reduction of worry symptoms post intervention at 9 months

• Patients' reduction of depressive symptoms post intervention at 9 months

• Patients' reduction of the use of psychiatric medication post intervention at 9 months

• Patients' increase in quality of life post intervention at 9 months

• Patients' reduction in use of health service post intervention at 9 months

• Patients' reduction in leave of absence from work post intervention at 9 months

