### Secondary outcome measures

Depressive symptoms will be measured by the validated Chinese version of the Centre for Epidemiological Studies-Depression Scale (CES-D) [19]. Health related quality of life will be measured by the validated Chinese version Medical Outcomes Study Short-Form Health Survey (SF-12) [20]. The SF-12 is a 12-item survey that reports health-related quality of life, including both physical and mental functioning and well-being. It has shown to be a valid measure for measuring health related quality of life in local Chinese population.

"Mindfulness" will be measured by the Five Facet Mindfulness Questionnaire [21].

Health service utilization and medication use: Utilization of health services including visits to primary care doctors (both private and public) and hospitalizations and the number of days of absence from work attributable to anxiety will be recorded at 4 weekly intervals by the trained research assistant using telephone. The frequency and duration of practice of both MBSR and PEG in each group will be documented by a Weekly Homework Form that will be collected each week during class and at 3 month interval until the end of 9 month post intervention. Moreover, medication use including changes in medication will be monitored at 3 month interval. Response rate (enrolment of subjects), retention rate (number and proportion attended each class) of the MBCT and the psycho-education group will be documented.

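### As worded, the covariate rule for the secondary repeated-measures model permits adjustment for post-randomisation outcomes, and on any reading it picks covariates by significance

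*Protocol article*

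**What the plan says.** All the analysis text is in the protocol article, section Data and statistical analysis.

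- Secondary model: "the three groups will be simultaneously taken into the analysis of variance model for repeated measures".
- Its covariates: "The baseline measurement of anxiety symptoms and any significant secondary outcome variables will be entered into the model as a covariate". The part at issue, with the reason given for it, reads "any significant secondary outcome variables will be entered into the model as a covariate as they are considered to be confounders".
- Definition of the secondary outcomes, a few lines above: "Secondary outcomes included the change in scores of CES-D and SF-12".
- Covariates of the primary ANCOVA, in a parallel sentence: "the baseline anxiety score and other baseline characteristics that significantly difference between groups will serve as covariates".

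Under Secondary objectives, the protocol lists effects that MBCT is expected to have, among them "Patients' reduction of depressive symptoms post intervention at 9 months" and an increase in quality of life. Under Primary Objectives, the reduction of anxiety symptoms is also set at 9 months. The primary end point in the analysis section, however, is change from baseline to the end of the intervention.

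**The concern.** A secondary outcome as this section defines it is a change score, and a change score exists only after randomisation. Depression and quality of life are also things that MBCT is intended to change. A follow-up variable affected by treatment is a mediator or a parallel outcome. It cannot confound a randomised comparison. Conditioning on it takes out of the anxiety effect whatever is shared with that variable. The result is not the total effect of assignment. Without further assumptions about common causes of the two outcomes, it is not a clean direct effect either.

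The stakes go beyond a minor supporting analysis. The repeated-measures model is the only one described that uses the 3, 6 and 9 month data, and both the primary and the secondary objectives are set at 9 months. If the covariate rule admits post-randomisation outcomes, a treatment that also helps depression would look less effective on anxiety at the time point the objectives name.

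**Working it through.** **Step 1: what the sentence allows.** Two readings are open.

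- *Reading A: baseline qualifies anxiety only.* The secondary outcome variables then carry the section's own definition, change in CES-D and SF-12, and are post-randomisation. In support, the primary ANCOVA sentence says baseline for both of its items, while this one switches to the word outcome.
- *Reading B: baseline qualifies both items.* The covariates are then pre-randomisation. In support, the sentence opens with the words baseline measurement, and it runs parallel to the primary ANCOVA sentence.

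The text does not say when the variables are taken or what significant refers to, so it does not exclude Reading A.

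**Step 2: inputs.** From the sample-size paragraph: mean BAI change 5.6 for MBCT and 2.0 for the comparator (called the discussion group there and taken here as the psycho-education arm), SD 7.4, 76 per group. The planned difference is 5.6 − 2.0 = 3.6 points, or 3.6/7.4 = 0.486 SD.

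The documents give neither of the other two inputs, so both are assumptions: *r*, the within-arm correlation of the covariate with BAI change (0.3 to 0.7), and *d*, the standardised effect of MBCT on the covariate (0.2 to 0.486, the top value being equal to the planned effect on BAI).

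The plan states no figure for the secondary model, so there is none to reproduce. (The stated 76 per group does not follow from its inputs: 2 × (1.645 + 0.842)² × 7.4² / 3.6² ≈ 52.3, or 53 per group. This has no bearing on the present point.)

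**Step 3: Reading A.** Adjusted difference = 3.6 − *r* × 7.4 × *d*. For example, at *r* = 0.5 and *d* = 0.35: 3.6 − 0.5 × 7.4 × 0.35 = 2.31.

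| *d* | *r* = 0.3 | *r* = 0.5 | *r* = 0.7 |
|---|---|---|---|
| 0.2 | 3.16 (12% removed) | 2.86 (21%) | 2.56 (29%) |
| 0.35 | 2.82 (22%) | 2.31 (36%) | 1.79 (50%) |
| 0.486 | 2.52 (30%) | 1.80 (50%) | 1.08 (70%) |

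A simulation of 3,000 trials with 76 per arm at *r* = 0.5 and *d* = 0.35 gave 2.32, against 3.61 unadjusted.

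Two-sided 5% power at 76 per arm is 0.85 for the unadjusted 3.6 points. With the adjusted difference and standard error 7.4 × √(1 − *r*²) × √[(2/76)(1 + *d*²/4)], it is 0.59 at *r* = 0.5, *d* = 0.35 and 0.23 at *r* = 0.7, *d* = 0.486. The loss is not uniform. At *r* = 0.7, *d* = 0.2 power is still about 0.845, because the covariate also reduces residual variance. Even there, the estimate falls 29% short of the total effect.

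**Step 4: Reading B.** In the same simulation, adjusting for a baseline secondary variable correlated with BAI change gave 3.60 against 3.61 unadjusted. Nothing is removed.

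What remains under Reading B is the selection rule. Under randomisation, baseline variables differ between arms only by chance. A significance test is a poor way to choose among them, and it leaves the covariate set unknown until the data are seen.

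**The case against.** The strongest reply is that the authors simply meant baseline values. The sentence opens with baseline measurement, which can grammatically cover both items. The primary ANCOVA sentence follows the same pattern and is explicitly about baseline. The section says that psychological characteristics will be compared at baseline. The word confounders also fits adjustment for baseline imbalance better than adjustment for outcomes. All of this stands as a plausible reading, and under it no treatment effect is lost.

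A reader might therefore go too far in the other direction and infer that the plan does adjust for follow-up outcomes, or that a significant secondary outcome means one that responded to treatment. The documents do not establish either. Significant is undefined and could refer to a baseline difference, a correlation with anxiety or a treatment response.

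Two further limits stand. The sentence governs only the secondary analyses; the primary end-of-intervention ANCOVA uses covariates stated to be baseline. And the arithmetic describes two arms at one time point, not the three-arm repeated-measures model with baseline anxiety, so the percentages and power figures are illustrations. The 70% corner needs MBCT to beat a CBT-based active control on the covariate by as much as on BAI, together with a correlation of 0.7.

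The baseline reading does not, however, rescue the sentence. The section's own definition of secondary outcomes points the other way, so an analyst could follow the text to the letter and condition on follow-up CES-D. Nor is this a detail left to a later analysis plan: the protocol states a rule and a rationale for it.

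**Conclusion.** The covariate rule is defective as written. It permits adjustment for post-randomisation outcomes that the trial hopes to change, and it does not fix the covariate set on either reading.

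- If follow-up outcomes are entered, the BAI contrast with the active control shrinks from the planned 3.6 points to about 3.2 to 1.1 (12% to 70% removed). This rests on the assumed ranges for *r* and *d* and on a simplified contrast. The direction is towards zero whenever MBCT improves the covariate and improvement in it goes with improvement in anxiety.
- If only baseline values are entered, there is no such bias. The faults are then selection by significance and a confounding rationale that applies to a randomised comparison only as chance imbalance.

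The document does not show which of these will happen, so it cannot be said that the planned analysis will remove part of the effect. The primary end-of-intervention result is not touched. The point still matters because no other model described reaches the 9-month time of the stated primary objective.

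**What to change.** Replace the covariate sentence for the repeated-measures model so that it says three things:

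1. The model adjusts only for pre-randomisation variables named in advance: the baseline value of the outcome being analysed plus a short fixed list.
2. No covariate is selected by a significance test, and the statement that these variables are confounders is dropped.
3. No outcome measured after randomisation enters the model. Any analysis that adjusts for follow-up depression, quality of life or mindfulness is reported separately and labelled as a mediation analysis.

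If baseline values were meant all along, saying so and naming the variables settles the timing question. The change is one sentence, made before the analysis begins. It needs no extra data, visits or participants.

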## Research objectives

### Primary Objectives

The primary objective of the study is to evaluate the superior effects of MBCT in reducing anxiety symptoms in patients with generalized anxiety disorder from the community and primary care at 9 months when compared to Psycho-Education Group using cognitive behavioural therapy and Usual Care (UG) groups.

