## Limitations

Participants who volunteer for the study could be biased towards non-pharmacological treatment and those who are assigned to the usual care group may be disappointed and drop out from the study. Although we will offer MBCT at the end of the study, the attrition rate for this group of participants is likely to be higher. Further analysis of the demo-sociographic characteristics of pateints who enrolled in our study will further inform the generalizability of our findings.

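### Intention to treat is listed only as an additional analysis, and the only named model reaching 9 months is repeated-measures ANOVA, although higher dropout is expected in usual care

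*Protocol article*

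**What the plan says.** All the analysis statements are in the protocol article under *Data and statistical analysis*.

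- **Primary endpoint:** "Our primary end point is the change of anxiety and worry score (BAI and Penn State Worry Scale) from baseline to the end of intervention".
- **Primary model:** "For primary analyses, treatment outcomes will be assessed by ANCOVA". No analysis population is attached to it.
- **Longitudinal model:** "For secondary analyses, the three groups will be simultaneously taken into the analysis of variance model for repeated measures".
- **ITT:** mentioned once, after both models: "Analysis will also be performed on an 'intention to treat' analysis".

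Two other sections bear on the point. *Primary Objectives* sets the comparison at a later time: "from the community and primary care at 9 months when compared to Psycho-Education Group". *Limitations* foresees that "those who are assigned to the usual care group may be disappointed and drop out from the study", and that "the attrition rate for this group of participants is likely to be higher". No attrition rate is given. *Methods and Design* lists one baseline and four follow-up assessments: end of intervention, then 3, 6 and 9 months later.

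**The concern.** Two stated choices combine badly with a stated expectation.

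The first choice is the rank of ITT. If ITT is what will *also* be done, the analyses named before it are, on a plain reading, something else. That leaves room to report a non-ITT result first.

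The second is the longitudinal model. Conventional repeated-measures ANOVA needs a complete set of visits from each participant. It is called secondary, but the primary ANCOVA stops at the end of intervention, so this is the only named model that can address the 9-month objective, and loss has had the longest time to build up by then.

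The expectation is that usual-care participants will leave more often because of the arm they were given. Loss that depends on the arm, and perhaps on outcome, breaks the comparability that randomisation created. At stake is bias in the MBCT versus usual-care contrast. Loss of power matters less.

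**Working it through.** **1. The plan's own figure.** The article gives 76 per group and no dropout allowance. Its inputs are BAI changes of 5.6, 2.0 and 1.1 (SD 7.4), one-sided 5% and 80% power. For the smaller difference, 5.6 - 2.0 = 3.6:

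n = 2 × (1.645 + 0.842)² × (7.4 / 3.6)² = 52.2, so 53 per group.

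Two-sided 5% gives 67. The stated inputs do not reproduce 76. The figure would fit 53 / (1 - 0.30) = 75.7, but a 30% allowance is nowhere stated. This is a separate matter. It matters here only because the article supplies no dropout rate, so every rate below is an assumption.

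**2. Bias in a completers' contrast.** Let change be the reduction in BAI, d the proportion lost in an arm, and g the mean change of stayers minus that of leavers. The whole-arm mean is (1 - d) × stayers + d × (stayers - g) = stayers - d × g. Stayers therefore overstate their arm's mean by d × g, and

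shift in (MBCT - usual care) = d_MBCT × g_MBCT - d_UC × g_UC.

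The planned contrast is 5.6 - 1.1 = 4.5. Take g as 3.7 points in size (half of the SD of 7.4):

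| Loss MBCT / UC | g MBCT | g UC | Shift | Share of 4.5 |
|---|---|---|---|---|
| 10% / 10% | 3.7 | 3.7 | 0.37 - 0.37 = 0 | 0% |
| 10% / 30% | 3.7 | 3.7 | 0.37 - 1.11 = -0.74 | -16% |
| 10% / 30% | 3.7 | 0 | 0.37 - 0 = +0.37 | +8% |
| 10% / 30% | 3.7 | -3.7 | 0.37 + 1.11 = +1.48 | +33% |

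In these rows MBCT leavers do worse than MBCT stayers. Reversing both signs of g reverses the sign of the shift. The direction cannot be settled from the document.

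**3. Complete data over four follow-up visits.** If each visit is missed independently with probability q, the share with all four is (1 - q)⁴:

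| q (assumed) | (1 - q)⁴ | Of 76 per arm |
|---|---|---|
| 5% | 0.815 | about 62 |
| 8% | 0.716 | about 54 |
| 10% | 0.656 | about 50 |

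This applies to repeated-measures ANOVA fitted in the conventional way, not to the primary ANCOVA, which needs only the 8-week score.

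**4. Power at the primary time point.** At 8% loss by week 8, 0.92 × 76 = 70 remain per arm. Two-sided t-test power for a difference of 3.6 (SD 7.4) is then 81.5%, against 84.6% with all 76. For MBCT versus usual care (4.5) with 10% and 30% loss, two-sided power is about 91%. Power is not the main problem.

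**The case against.** **Completers are never mentioned.** A reader might infer that the lead results are known to rest on self-selected completers, or that poor attenders will be excluded. The document does not support either reading. It names no completer, per-protocol or attender set and no exclusion rule, and *Secondary outcome measures* says only that class attendance will be documented. *Also* may be loose wording for ITT throughout, in a paragraph that is loosely worded elsewhere. This objection stands against the strong reading. It does not remove the ambiguity, because as written ITT comes after the other analyses and is additional to them.

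**Repeated-measures ANOVA is secondary.** This is correct, and the 8-week ANCOVA is not subject to four-visit deletion. The model still matters because the primary objective is set at 9 months and no other named model gets there.

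**Power.** A reader might put the four-visit figure of 54 per arm into the sample-size comparison and conclude that power drops to about 70%. That joins the completeness of one model to a two-group test at another time point. It is the power of neither analysis. Step 4 of the working gives the relevant figures.

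**Missing-data rules may be in a document not shown.** This is fair for imputation details and for exactly how the ANOVA would be fitted. The point does not rest on their absence. It rests on the rank given to ITT and the model named, both of which are stated.

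**The bias is hypothetical.** Rates and gap are assumed, the shift can be zero, and the article does not say that the extra loss happens by week 8. The sponsor also acknowledges the risk and offers usual-care participants MBCT at the end of the study. All of this limits what can be said about size. The Limitations section nevertheless still expects higher attrition in that arm after mentioning the offer.

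**A mixed model is not a full cure.** With baseline as a covariate, it gains nothing from a participant who has no follow-up score. This stands, and is why the fix includes a further sensitivity analysis.

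**Conclusion.** The concern holds in a limited form. The plan ranks ITT as an additional analysis, leaves the population of the primary ANCOVA unnamed, and chooses for its only 9-month model one that conventionally discards participants with any missed visit. It does so while expecting allocation-related, unequal dropout. Whether the lead results would in fact come from completers cannot be known from the document.

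Under assumed losses of 10% and 30% and a 3.7-point gap, a completers' contrast of MBCT with usual care would move by about -0.7 to +1.5 BAI points against a planned 4.5. Equal loss with equal gap gives no shift. Neither size nor direction can be fixed from the article. The risk is bias; at the primary time point power stays adequate under the losses examined.

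**What to change.** 1. State that the primary analysis is by ITT: every randomised participant, in the arm assigned, however many sessions were attended.
2. Replace repeated-measures ANOVA with a likelihood-based mixed model that uses every available visit, with arm, visit, arm-by-visit interaction and baseline score.
3. Label any completer or attender analysis as a sensitivity analysis.
4. Add one missing-not-at-random sensitivity analysis. The mixed model assumes data missing at random and does not recover participants with no follow-up score.

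If ITT was meant throughout, item 1 is a one-sentence clarification. The cost is wording and a little more analysis work, with no extra patients or data. The downside is that the estimate may be less favourable than a completers' result would have been.
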